**Fig. 2 fig2:**
[figure not shown]
Nurse AMIE assesses symptoms daily to sustain patient engagement and guidelines-concordant interventions.

### Collecting data from patients

2.8

In a previous study in which we used a tablet-version of Nurse AMIE, the device allowed patients to record relevant data including daily symptom questions (fatigue, sleep, distress, and pain) and step counts. The tablet version also recorded the use of each of the intervention modules, and time spent within a given module. The Nurse AMIE for Amazon Echo Show extended this functionality so patients could record data using the voice interface. Nurse AMIE would ask how many steps the participant took, and the participant would say the number to enter it in. Using a voice interface could lower participant burden, and streamline the data collection process. Furthermore, collected data could be used by the Nurse AMIE skill to dynamically recommend relevant interventions. For example, if a patient indicated high levels of distress, the skill could suggest an appropriate intervention for coping with symptoms, such as soothing music. We also incorporated questions from the Patient-Generated Subjective Global Assessment (PG-SGA) short form into Nurse AMIE; the full survey was asked monthly [11,12].

### Sharing data with facilitators and clinicians

2.9

The patient data collected by Nurse AMIE were automatically uploaded to an investigator-facing dashboard. As with the tablet version, the data were reviewed daily by study facilitators, discussed with patients in weekly calls, and could be shared with clinicians through the electronic medical record when elevated symptoms were reported. Discussion with study clinicians led us to set a threshold of 7 or more out of 10 to define ‘elevated symptoms’. Elevated levels of pain or distress were relayed to the patient's oncologist at the time of patients reporting.

### Adding nutrition education and support to nurse AMIE

2.10

The overall goal of the new nutrition module was to provide evidence-based information about nutrition to MBC patients. The nutrition advice provided was largely based on American Institute for Cancer Research materials [13]. The module included healthy recipes in the pink ribbon menu on the device, and daily nutritional strategies. Nutrition strategies included tips to deal with side effects of cancer and its treatment, tips regarding medications/cancer treatment and possible interactions with nutrition, and tips providing information on weight monitoring, appetite and weight loss. This nutrition content was developed based on the needs that MBC patients have reported previously [7].

We worked as a team to discern whether it was possible to develop a question and answer section where MBC patients could pose questions on nutrition, which would either be answered directly by the Alexa system, or Alexa would “forward” the questions to the facilitators. Based on our initial exploration, it was not feasible to develop this section within our timeline, and we will need to wait for future funding opportunities to implement this section.

### Intervention delivery: nurse AMIE for Amazon Echo Show

2.11

Participants were provided an Amazon Echo Show, along with a pedometer, set of resistance bands, and participant binder. Materials were shipped to participants, and participants engaged in an orientation session once they received these materials. The participant binder included care team and palliative care team information, instructions for the Amazon Echo Show and Nurse AMIE, instructions for the pedometer, step log sheets, and paper copies of instructions on the exercises. Instructions for exercises were also included as videos in the Nurse AMIE skill.

Exercise content was customized during onboarding based on the participant's metastases location. For example, if there were no bone metastases, there was a three-level exercise program that included upper and lower body exercises that can be done standing. For patients with bone metastases, the exercise programs were more restrictive. For participants with lower extremity bone metastases, there was a chair exercise program only. For participants with spinal metastases, there was a three-level program that avoids spinal twisting motions. For participants with upper body bone metastases, there was a three-level program that avoided stressing the arms and upper torso.

### Protection of confidentiality

2.12

Two actions were taken to protect confidentiality of the participants while using the Alexa Echo Show. First, no participant provided their actual names or identifying information within the Nurse AMIE platform. Additionally, the participants were instructed to go through the settings in the Amazon Alexa Echo Show device and select the option to ensure no voice recordings were made. Participants were given an alternate email address and identification to be used within the Nurse AMIE for Amazon Echo Show platform. Study team members created the accounts and provided the information to participants.

### Daily interactions with nurse AMIE for Amazon Echo Show

2.13

To start an interaction with Nurse AMIE, the participant would say “Alexa, Open Nurse AMIE.” The opening screen depicted a nurse waving hello, with a unique spoken greeting for each day of participation. Following the greeting, a nutrition message appeared on the screen, and Nurse AMIE read it aloud to the participant. An external link to a recipe accompanied the nutrition tip, and the participant had the option to visit the recipe at that time, or later in the pink ribbon menu. All of the nutrition education messages, along with links to the informational websites, and healthy recipes presented in categories (e.g., breakfasts, soups and salads, vegetarian) were included in the participant binder. Immediately following the nutrition message, the participant answered the daily symptom questions (rating pain, sleep, fatigue, and distress) on a 0–10 scale. If the answer to the questions about pain or distress were above the *a priori* set clinical threshold of 7 out of 10, the study facilitator contacted the clinical medical team to alert them of the participant's response.

Data from the daily symptom questions fed into a decision algorithm, which determined which type of self-care intervention to offer the participants. Once offered, participants then verbally indicated wanting or not wanting to access that intervention. The algorithm was developed for the tablet-based version of Nurse AMIE, and not changed for the Alex Echo Show version. If participants declined the intervention, they were reminded they can choose their own intervention verbally by instructing Nurse AMIE to “open the pink ribbon menu,” and select their preferred intervention. The Nurse AMIE interventions include exercise videos (strength, stretching, and balance), symptom management education (cognitive behavioral therapy modules), soothing music, guided relaxation, and recipes.

### Dashboard and study facilitator calls

2.14

An investigator-facing dashboard was developed for Nurse AMIE that allowed study facilitators to review the symptom responses, and which Nurse AMIE interventions were used by participants daily. While receiving Nurse AMIE, the study facilitator called the participant weekly. These weekly calls were set up on a day and time of the participants' choosing. The study facilitator asked them how they were feeling, reviewed elevated symptom responses, and asked if they were having any difficulties or questions about the program. The facilitator also reviewed lifestyle activities the participants were using to manage their symptoms. Additionally, the facilitator provided the participants with an updated individualized step goal based on the steps the participants had recorded using the Nurse AMIE platform. The facilitator averaged the daily steps over the previous week, and set the step goal as that value plus 500 steps. At the end of each week, participants were asked to complete a more in-depth symptom report, the PG-SGA Questionnaire [14]. Nurse AMIE read the questions to the participant. The system has built in skip logic, so questions only appeared if they were required based on the previous answer. Once the participants completed the study, the Nurse AMIE skill was disabled and removed from the participants’ device, and they no longer received messages/interventions from Nurse AMIE.

### Outcomes

2.15

Patient acceptability was defined as the percentage of eligible and approached participants agreeing to participate in the intervention. We observed an acceptability of 68% with the tablet-based Nurse AMIE intervention, and we hypothesized the Nurse AMIE for Amazon Echo Show version would have a comparable or higher acceptability rate [8]. We defined feasibility the same as the tablet-based Nurse AMIE intervention: participating in at least 30 of the first 90 days. We observed that 86% of our participants in our prior studies that used a tablet version of the intervention achieved this definition of feasibility. We anticipate it would be equally high if not higher with the Amazon Echo Show version.

Patient reported outcomes measures included the 36-Item Short Form Survey (SF-36), the Brief Pain Inventory (BPI), Brief Fatigue Inventory (BFI), PROMIS sleep disturbance measure (PROMIS SF v1.0 - Sleep Disturbance 8b), and a measure of distress used at the Penn State Cancer Institute [[15], [16], [17], [18]]. Outcomes were assessed at baseline, the end of month three, and end of month six. Additionally, assessments related to the usability of Nurse AMIE were collected at the end of month three and six, and included: a User Version of the Mobile Application Rating Scale (U-MARS), System Usability Scale (SUS), Client Satisfaction Questionnaire (CSQ-8), Credibility and Expectancy Questionnaire (CEQ), and Technology Acceptance Model (TAM) [[19], [20], [21], [22]]. Participants completed these outcome questionnaires over Zoom.

### Sample size

2.16

Based on previous data from the tablet version of Nurse AMIE, the standard deviation for physical distress in MBC patients at baseline was 1.9 units, on a scale of 0–10, and the change over three months was 2.7. To be conservative, we consider the difference of outcome change over three months between two groups as 1.8 (effect size = 0.95). Using a power level of 0.80, and setting (two-sided) α at 0.05, 18 participants per group provided sufficient power to detect the expected between-group difference. Given the potential for disease progression that would prevent continued participation in this population, we anticipated a loss to follow-up of approximately 15%. As such, we recruited 21 participants per group.

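### The sample size calculation standardises a difference in three-month change by the baseline SD, so the stated 0.80 power depends on an unstated SD of change

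*Protocol article*

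**What the plan says.** Section 2.16 (Sample size) takes its inputs from the earlier tablet study. The only SD printed is a cross-sectional one: "the standard deviation for physical distress in MBC patients at baseline was 1.9 units", on a 0–10 scale. The same sentence adds that "the change over three months was 2.7". The planned effect follows: "we consider the difference of outcome change over three months between two groups as 1.8 (effect size = 0.95"). With the error rates given as "Using a power level of 0.80, and setting (two-sided) α at 0.05", the section concludes that "18 participants per group provided sufficient power to detect the expected between-group difference". After allowing for loss to follow-up, 21 per group were recruited.

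The Abstract (Methods) defines the primary outcome as change in physical distress over three months. Section 2.18 (Statistical analyses) names a two-sample *t*-test or Wilcoxon rank sum test as the primary between-group analysis. Mixed models are also planned. The covariates listed for them are age, cancer treatment type and cancer treatment duration; the starting distress score is not among them.

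**The concern.** The numerator of the effect size is a difference in change, but the denominator is the spread of a single measurement. A two-sample test on change scores has its power set by the SD of the change score. That SD equals the baseline SD only in a special case: with equal SDs at both times, when the two measurements correlate at exactly 0.5. It is larger when the correlation is lower and smaller when it is higher.

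The article does not say that 1.9 is also assumed for change, so the stated power does not follow from the printed inputs. Two uses of the figure are affected. A non-significant result would be read against a claimed 80% power that may not have applied. The same calculation could also be carried into later Nurse AMIE studies, which the Discussion says this pilot will inform.

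**Working it through.** **Inputs from section 2.16.** Difference in three-month change 1.8; SD 1.9 (baseline); power 0.80; two-sided α 0.05; 18 evaluable per group.

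**Assumed, because the article does not give it.** The correlation r between the start and end of the three-month window, taken over a range, with an SD of 1.9 at both times unless stated otherwise.

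**Step 1: reproduce the plan's figure.** 1.8/1.9 = 0.947, which rounds to 0.95. The normal-approximation sample size is n = 2(1.960 + 0.842)² × (1.9/1.8)² = 2 × 7.849 × 1.114 = 17.5, so 18 per group. The arithmetic is therefore correct for the inputs used, and it confirms that the baseline SD is the denominator. Power at 18 per group with SD 1.9 is 0.811 by the normal approximation and 0.788 by the noncentral *t*.

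**Step 2: the SD that the test needs.** For equal SDs, SD of change = 1.9 × √(2(1 − r)). At r = 0.5 this is 1.9 × √1 = 1.9.

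**Step 3: power with that SD** (noncentral *t*, difference 1.8, 18 per group):

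| r | SD of change | Effect size | Power | n per group for 0.80 |
|---|---|---|---|---|
| 0 | 2.69 | 0.67 | 0.50 | 36 |
| 0.3 | 2.25 | 0.80 | 0.65 | 26 |
| 0.5 | 1.90 | 0.95 | 0.79 | 19 |
| 0.7 | 1.47 | 1.22 | 0.95 | 12 |

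**Step 4: break-even.** Power of 0.80 at 18 per group needs an SD of change of at most 1.87 (noncentral *t*) or 1.93 (normal approximation). With equal SDs this means r of at least 0.51 or 0.49. If the month-3 SD differs from 1.9, r = (1.9² + s² − 1.87²)/(2 × 1.9 × s), where s is the month-3 SD. This gives about 0.41 for s = 1.5 and 0.62 for s = 2.3.

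**Step 5: baseline-adjusted alternative.** In an ANCOVA with equal SDs, the residual SD is 1.9 × √(1 − r²), which never exceeds 1.9. Power at 18 per group is 0.79 at r = 0, 0.82 at r = 0.3 and 0.89 at r = 0.5. The degree of freedom spent on the covariate changes these by less than 0.001.

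**The case against.** The best defence has four parts.

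- **The arithmetic is right and the implied assumption is ordinary.** Taking the SD of change as roughly equal to the baseline SD is exact at r = 0.5 with equal SDs, and nothing in the article favours a lower r over a higher one. This stands. It means that the direction of the error is unknown, and the point cannot be put as a claim that the trial is underpowered.
- **The effect was already shrunk.** The tablet study's change was 2.7, and 1.8 was chosen to be conservative. If the difference were 2.7 with no change in controls, power at 18 per group would be 0.83 at r = 0 and 0.94 at r = 0.3. This is fair reassurance about a large effect. It does not make 0.80 the power to detect 1.8, which is what the section claims.
- **The full protocol may give the SD of change.** It may, and its absence from a condensed article would not be a finding by itself. But the article prints a specific calculation whose printed SD does not match its outcome, and that mismatch is open to comment.
- **This is a fully enrolled pilot.** The choice of SD biases no estimate and does not affect type I error, and the article already lists the small sample as a limitation. This lowers the severity but does not remove the need to correct a formal power statement.

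The planned mixed models do not answer the point, because the primary test is unadjusted and the starting score is not a listed covariate.

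**Conclusion.** The concern holds, at moderate severity. The stated 0.80 power at 18 per group is conditional on an SD of change of about 1.9 or less. With equal SDs at both times, that is a correlation of about 0.5 or more; with month-3 SDs of 1.5 to 2.3, the threshold runs from roughly 0.4 to 0.6. Over r = 0 to 0.7 and equal SDs, actual power runs from 0.50 to 0.95. Both r and the equality of the SDs are assumptions, not figures from the article.

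Three stronger readings are not supported:

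- **That the trial is underpowered.** The article gives no r, and above about 0.5 the plan is adequate or generous.
- **That 2.7 is the SD of change.** The sentence is terse enough to allow this, but moving from 2.7 to a smaller difference of 1.8 in order to be conservative makes sense only if 2.7 is a mean change.
- **That 21 per group is too few for the stated attrition.** 18/0.85 = 21.2, but the loss is given only as approximate. Losing 3 of 21 is 14.3% and leaves exactly 18.

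**What to change.** 1. **Restate the power in section 2.16.** Use the SD of three-month change, or r, from the tablet study, and report the power for a difference of 1.8 at 18 per group. If neither can be recovered, give the range in the table above as conditional on r and say that equal SDs are assumed. Replace the statement that power is sufficient with that figure or range.
2. **Adjust the primary comparison in section 2.18 for the starting score.** Compare distress at the end of the three-month window by ANCOVA, with the score at the start of the window as covariate. Under equal SDs of 1.9, power at 18 per group is then about 0.79 or more whatever r is, so the calculation no longer depends on an unknown correlation.

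No more patients are needed and, since distress is already collected at baseline and at months three and six, no new measurements either. The first change costs one recalculation and may give a less favourable stated power. The second is a small but real change to the named primary test. It should be made and documented before the group comparison is run.

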### Data and safety monitoring

2.17

The study facilitators reviewed the daily symptom data on the dashboard daily. Adverse events were formally assessed monthly, using the National Institute of Heath developed PRO-CTCAE measure [23]. In the unlikely event an unanticipated adverse event were deemed to be definitely related to the study occurred, the relative merits and risks of continuing the research would be discussed with the treating physician. The Data Safety Monitoring Committee of the Cancer Institute would be informed of any such actions, but none occurred.

### Statistical analyses

2.18

Data analyses will be performed using SAS version 9.4. Summary statistics including mean and standard deviations for continuous variables and frequency with percentage for categorical variables are reported. The normality assumption for outcome variables is assessed by group based on Shapiro Wilk tests, and the skewness and potential outliers of data distribution will be evaluated to see if any transformation will be needed. Between group (immediate AMIE baseline to month three, and delayed AMIE month four to six) comparison will serve as the primary analyses, where two-sample *t*-tests or Wilcoxon rank sum tests will be used, as appropriate. To further provide evidence informing potential future studies, or may point towards temporal trends or variability in each group, changes within-group (baseline to month three, month four to six) will also be explored mainly with summary statistics. Generalized linear mixed effect models for group comparison will be fitted, and the variables of age, cancer treatment type, and cancer treatment duration will be initially examined and controlled. If we detect some baseline characteristic variables showing unbalanced between two groups, we will consider them in the regression, and report them. The amount of missing data will be reported, which is expected to be minimal due to previous data collection experience. We will try best to collect the data, and report the number of missing data and mechanisms for this missing data (e.g., loss to follow-up, technical errors). If any missing data exist, the missing mechanism will be evaluated. Based on previous work and previous versions of this trial on the tablet, it is reasonable to assume that data will be missing at random (MAR), under which the likelihood based analyses will yield valid estimates and valid inference.

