**Methods:**

Nurse AMIE (Addressing Metastatic Individuals Everyday) is a technology based supportive care platform that provides guideline-concordant symptom management interventions in response to patient reported symptoms. We have previously successfully implemented a tablet version of Nurse AMIE. However, some eligible patients chose not to participate because they were overwhelmed by the technology. To address this barrier, we translated the Nurse AMIE platform to the Amazon Echo Show, which allowed for voice-based interactions. Forty-two MBC patients were randomized 1:1 to receive the Nurse AMIE for Echo Show immediately for six months, or to receive the same intervention for three months, after a three month delay. The primary outcome was change in physical distress over three months, and secondary outcomes included feasibility, acceptability, patient reported outcomes and usability.

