### Randomization and blinding

2.4

During baseline assessments, participants were randomized using a random sequence generated by a researcher not involved in data collection. Conditions (Immediate AMIE or Delayed AMIE) were blindly placed in sealed envelopes, and not opened until baseline assessments were completed. Randomization was not stratified. Participants were not blinded to their group assignment. Study team members involved in patient-facing work, such as the study-facilitator calls, were also not blinded to group assignment. The principal investigator was blinded to participant allocation, and all study analyses will be performed by study team members blinded to group status.

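### The primary test of change does not condition on baseline distress, and the choice of test and some supporting covariates is left to the data; one prespecified ANCOVA would be more precise once the compared periods are reconciled

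*Protocol article*

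**What the plan says.** The abstract of the protocol article defines the endpoint: "The primary outcome was change in physical distress over three months". Section 2.18 (Statistical analyses) makes a between-group t-test or Wilcoxon rank sum test the primary analysis, whichever is judged suitable. On how that is judged, it says "The normality assumption for outcome variables is assessed by group based on Shapiro Wilk tests", and adds that skewness and outliers will be examined to see whether to transform. No cut-off or decision rule is given.

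Mixed models are then fitted in addition. For these, "the variables of age, cancer treatment type, and cancer treatment duration will be initially examined and controlled", and further variables may follow: "If we detect some baseline characteristic variables showing unbalanced between two groups, we will consider them in the regression". Baseline distress is not on the named list, although section 2.15 has outcomes assessed at baseline. Section 2.4 states: "Randomization was not stratified".

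Section 2.18 also describes the primary comparison as the immediate arm from baseline to month three against the delayed arm in months four to six.

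**The concern.** Baseline distress is measured before randomisation and is likely to predict month-3 distress. A change score gives it a fixed coefficient of 1. ANCOVA estimates that coefficient, which under equal variances equals the correlation r. Whenever r is below 1, the change score over-corrects any chance baseline difference and has the larger variance.

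Two choices are also left to the data. The t-test addresses a difference in means and the Wilcoxon test a shift in ranks, so choosing between them after looking leaves the primary estimand open. In the supporting model, observed imbalance is a poor reason to add a covariate: in a randomised trial it arises by chance and says nothing about prognostic strength.

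At stake are precision in a trial planned on 18 evaluable patients per arm, conditional bias when the arms happen to differ at baseline, and a primary result whose definition is not settled in advance.

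**Working it through.** **Inputs.** Section 2.16 gives a between-group difference in three-month change of 1.8, two-sided alpha 0.05, and an SD described thus: "the standard deviation for physical distress in MBC patients at baseline was 1.9 units, on a scale of 0–10". It concludes: "Using a power level of 0.80, and setting (two-sided) α at 0.05, 18 participants per group provided sufficient power". The correlation r between baseline and month-3 distress is not given, so 0.3, 0.5 and 0.7 are assumptions.

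**The plan's own figure.** Effect size 1.8/1.9 = 0.947. By normal approximation, n = 2(1.960 + 0.842)²(1.9/1.8)² = 17.5, so 18 per arm, with power 0.811. The noncentral t gives 0.788. The stated 18 reproduces. It uses a baseline SD for a difference in change, which is the SD of change only if r = 0.5 with equal variances.

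**Change score against ANCOVA**, taking 1.9 as the SD at each visit and n = 18 per arm:

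- Change: SD = 1.9√(2(1−r)), 34 df.
- ANCOVA: residual SD = 1.9√(1−r²), 33 df, variance inflated by 1 + 1/(2n−4) = 1 + 1/32.
- Variance ratio before inflation: (1−r²)/(2(1−r)) = (1+r)/2.

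| r (assumed) | SD of change | Power, change | ANCOVA residual SD | Power, ANCOVA | Variance ratio |
|---|---|---|---|---|---|
| 0.3 | 2.25 | 0.65 | 1.81 | 0.81 | 0.65 |
| 0.5 | 1.90 | 0.79 | 1.65 | 0.88 | 0.75 |
| 0.7 | 1.47 | 0.95 | 1.36 | 0.97 | 0.85 |

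**If 1.9 is instead the SD of change**, the change-score test has power 0.79 whatever r is. ANCOVA has 0.92, 0.88 and 0.84 at r = 0.3, 0.5 and 0.7, and 0.80 at r = 0.9.

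**Break-even.** The inflation cancels the gain when (1+r)/2 × 33/32 = 1, that is r = 64/33 − 1 = 0.94. A search on power under the SD-of-change reading also gives about 0.94.

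**Chance imbalance.** The standard error of the baseline difference is 1.9√(2/18) = 0.63. A difference at least that large, in either direction, occurs in about one trial in three. The change score over-corrects by (1−r) times the imbalance. For a one-standard-error imbalance at r = 0.5 that is 0.5 × 0.63 = 0.32 units, or 0.32/1.8 = 18% of the target difference.

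**Pre-test.** Type I error was simulated (10,000 runs, 18 per arm) for a rule that uses Wilcoxon if Shapiro-Wilk rejects at 0.05 in either arm and the t-test otherwise. The 0.05 cut-off is an assumption.

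| Data | Type I error of the two-step rule | t-test alone | Runs sent to Wilcoxon |
|---|---|---|---|
| Normal | 0.052 | 0.050 | 10% |
| Normal, rounded to integers | 0.058 | 0.056 | 29% |
| Exponential | 0.047 | 0.045 | 95% |

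The error rate barely moves, but the test actually used varies widely with the shape of the data. The simulation did not include a data-driven transformation.

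**The case against.** Several stronger readings are tempting, and the document does not support them.

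- **That the primary test ignores baseline.** It does not: change subtracts each patient's starting value. For a concurrent randomised comparison, an unadjusted test of change is valid and unbiased on average. The loss is in precision and in bias conditional on the observed imbalance.
- **That covariates are chosen only by imbalance.** Three are named in advance. The imbalance rule adds to them, and it belongs to the supporting mixed model, so it cannot affect the error rate of the primary test.
- **That data-driven choice undermines the 5% level.** The simulated two-step rule stays between 0.047 and 0.058, close to the t-test alone in each case. Section 2.4 also has analysts blinded to group status, which limits deliberate steering.
- **That ANCOVA is free.** It costs one degree of freedom and a small variance inflation, and its gain depends on an unstated correlation. Part of the low 0.65 at r = 0.3 comes from using a baseline SD in section 2.16, which is a separate sample-size matter.

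The strongest objection is that these power figures concern a different comparison from the one written. Section 2.18 sets the immediate arm's first three months against the delayed arm's months four to six. The delayed arm's starting score would then be a post-randomisation value, and neither (1+r)/2 nor the premise of pure chance imbalance carries over. This stands. The gain applies to the concurrent baseline-to-month-3 comparison, and ANCOVA does not repair mismatched periods.

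It is also fair that this is a condensed article on a pilot. A decision rule for the tests, or the way baseline enters the mixed model, may be set out in a fuller plan. But the article itself names the unadjusted test as primary, and that choice can be judged as it stands.

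**Conclusion.** The point holds as one of efficiency and prespecification. The named primary test does not condition on baseline distress, no model lists it as a covariate, the choice between two tests with different estimands is left open, and the supporting model carries an imbalance trigger.

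For the concurrent comparison, ANCOVA would cut the variance by 35%, 25% or 15% at r = 0.3, 0.5 or 0.7, before the small finite-sample penalty. The power gain is about 16, 9 and 2 percentage points respectively. These figures assume 18 evaluable per arm, a difference of 1.8, SD 1.9 at both visits and the stated values of r. The direction holds for any r below about 0.94; the size does not.

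A reader might infer that the trial's type I error is compromised or that the primary test is invalid for want of adjustment. Neither follows from the evidence here.

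**What to change.** 1. Reconcile the periods in section 2.18 with the primary outcome in the abstract, so that the primary comparison is the concurrent randomised one from baseline to month 3. The remaining steps depend on this.
2. Prespecify one primary model: month-3 physical distress on group and baseline physical distress, by ANCOVA or an equivalent mixed model, reporting the adjusted mean difference and its 95% confidence interval.
3. Keep the Wilcoxon test as a sensitivity analysis only, and do not let a normality test select the primary method.
4. Give the supporting model a fixed covariate list and delete the imbalance trigger.

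Steps 2 to 4 need only wording changes, no new data, and one degree of freedom in the primary model. Step 1 changes the stated primary comparison, so it is more than an edit, but the month-3 assessment it needs is already scheduled in section 2.15. Section 2.18 describes the analyses as still to come; the changes should be recorded before outcomes are examined by group.
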